### Confidentiality {27}

Participant identification numbers are used to track questionnaires and data collection documents. A password-protected file is maintained that associates the participant’s name with the participant’s study identification number. Access to electronic data is password-protected and restricted to the study team. Paper data are stored in a locked file cabinet. Paper data may be removed for the purpose of coding, data entry, or auditing only. When taking participant files to intervention visits and assessments, files are transported in a locked box. Upon reaching the destination, these boxes are brought into the building or residence with the interventionists. Also, interventionists’ files identify participants by first name and last initial only. Participant home addresses are not included in the files. The study’s research coordinators in California and Rhode Island work closely with the statistician and data manager to ensure the secure exchange and storage of all project databases and questionnaires. Data exchanged between study sites are de-identified, encrypted, and password-protected.

### Plans for collection, laboratory evaluation, and storage of biological specimens for genetic or molecular analysis in this trial/future use {33}

As noted above, participants are asked to give explicit consent for the DNA and RNA collection and use, and future research of data and samples. For DNA and RNA, the collected samples sit in the collection tube at room temperature for 2 h then are placed in a − 20 °C freezer for the first 24 h before moving to − 80 °C freezer.

## Statistical methods

### Statistical methods for primary and secondary outcomes {20a}

A multiple logistic regression analysis will be used to examine the effect of the treatment group on the proportion of women who develop GDM. The model will include site and covariates to adjust for pre-randomization variables that may relate to the outcome, including parity, age, education, income, smoking, race/ethnicity, BMI, and time since last pregnancy. The effects of the pre-pregnancy weight loss intervention on weight, eating, activity, and physiologic outcomes will be examined using a linear mixed model with fixed effects for treatment condition (the between-groups factor), time (baseline, 16 weeks, 26 weeks’ gestation), site, and baseline covariates. Linear regression and logistic regression analyses will be performed to address the possible effects of the intervention on cases of excessive GWG, gestational hypertension, cesarean delivery, and large for gestational age at birth and 6 weeks, with site and baseline covariates entered in the models. A multiple linear regression analysis will also be used to examine the effect of the treatment group on composite scores of adverse maternal/neonatal outcomes, and logistic regressions will be used to examine separate effects on offspring obesity and odds of exceeding the National Academy of Science guidelines, including the same covariates described above.

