### Risk factors for gestational diabetes

While prior GDM is perhaps the strongest risk factor for recurrence of GDM, maternal obesity is also strongly associated with developing GDM during pregnancy [35, 46]. Overweight and obesity affect an estimated 66% of adult women [47], and an estimated 5–12% of women with obesity develop GDM during pregnancy compared with 1–3% of women with normal weight [48]. In epidemiologic studies, the risk of GDM has been four to eight times higher in women with overweight/obesity than with normal weight [48]. A meta-analysis concluded that for every 1 kg increase in pre-pregnancy BMI, the prevalence of GDM was increased by 0.92% [49]. A BMI greater than 35 increases the risk of GDM by about 6-fold [29]. Independent of GDM, maternal obesity is also associated with several other adverse pregnancy outcomes, including preeclampsia, stillbirth, fetal macrosomia, cesarean delivery, and post-surgical wound infection [50, 51]. Obesity is one of the few modifiable risk factors for GDM.

Other risk factors for GDM have been reported in observational [52, 53] and clinical trial [54] studies and include maternal age > 35 [29] (5- to 6-fold increased risk) [54], having a first-degree relative with diabetes (2- to 3-fold increased risk) [28, 29, 54–56], fasting blood glucose of 100–125 mg/dl (7-fold increased risk) [28, 55, 56], HbA1c between 5.8 and 6.4 (5- to 8-fold increased risk) [29, 54], and previous infant with macrosomia (3- to 4-fold increased risk) [53, 54].

Race/ethnicity is another consistent predictor of GDM. People who report Hispanic ethnicity or Native American, Asian, and African-American race have consistently been found to have an increased risk of GDM and recurrent GDM compared with non-Hispanic white women [19, 57–59]. The reasons for the higher prevalence of GDM in non-white women remain unclear. Possible reasons include acculturation among migrant populations and greater exposures to stress, the obesogenic environment, high-energy-dense foods, and obesity [59].

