#### Demographics and medical/reproductive history

At baseline, participants complete a demographic questionnaire assessing age, race, ethnicity, and weight history (e.g., inter-pregnancy weight changes). Given prior relationships with GDM recurrence [148], extensive pregnancy history information (maternal and neonatal) are collected [149, 150]. At follow-ups, changes in smoking, prescription medications, unsafe dieting practices [117], job status, and participation in other weight loss programs, and changes in medical history are assessed. Pregnancy urine tests are used to assess pregnancy status at quarterly visits until conception. Pregnancy confirmation is documented through clinical ultrasound results.

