**Maternal physiology**					
HbA1c (screening then annually until conception)	X	–	–	–	–
GDM assessment	–	–	–	X	–
Glucose, insulin	X	X	–	X	–
Inflammatory factors	X	X	–	X	–
Lipids	X	X	–	X	–
Blood pressure	X	X	–	X	–

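### The covariates named for the primary GDM model include no baseline glycaemic measure, although fasting glucose is measured before randomisation; this costs some precision but causes no bias

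*Protocol article*

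**What the plan says.** Section {20a} of the protocol article sets the criterion for adjustment, "The model will include site and covariates to adjust for pre-randomization variables that may relate to the outcome", and then names the variables: "including parity, age, education, income, smoking, race/ethnicity, BMI, and time since last pregnancy". Fasting glucose, HbA1c and prior macrosomia are not among them.

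The section on risk factors for gestational diabetes cites several multiples of risk. Two concern variables already in the model: "A BMI greater than 35 increases the risk of GDM by about 6-fold" and "maternal age > 35 [29] (5- to 6-fold increased risk". Two concern variables that are not: "fasting blood glucose of 100–125 mg/dl (7-fold increased risk" and "previous infant with macrosomia (3- to 4-fold increased risk". It also cites HbA1c of 5.8 to 6.4 at 5- to 8-fold and a first-degree relative with diabetes at 2- to 3-fold. It gives no multiple for education, income or smoking.

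Table 3 marks glucose at baseline ("Glucose, insulin X X – X", the first mark being baseline), and the outcomes section says that this is fasting glucose. On obstetric history, the protocol says that "extensive pregnancy history information (maternal and neonatal) are collected"; macrosomia is not named as an item. The primary outcome is defined in section {12} by glucose thresholds, and the fasting value is one of the four OGTT values.

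**The concern.** The list is meant to hold baseline variables that may relate to GDM. Fasting glucose meets that criterion on the protocol's own evidence, and its cited multiple is at least as large as those for age and BMI, which are listed. It is also one of the closest available baseline counterparts of the outcome, since both are glucose measurements, although the baseline value is taken before pregnancy.

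In a randomised trial a strong baseline predictor is included for efficiency. Adjustment corrects for chance imbalance in that predictor and usually makes the test of treatment more powerful. The primary analysis rests on about 176 pregnancies and a stated power of 81.98%, so there is little margin. The variable is already collected, so leaving it out saves nothing in data collection.

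**Working it through.** **1. The plan's own figure.** Inputs from section {14}: 88 per group, 60% versus 38%. The test level is not stated; two-sided 5% is assumed.

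- Pooled test of proportions: null SE = √(2 × 0.49 × 0.51 / 88) = 0.0754; alternative SE = √((0.60 × 0.40 + 0.38 × 0.62) / 88) = 0.0735. z = (0.22 − 1.96 × 0.0754) / 0.0735 = 0.98, so power is 83.7%.
- Wald test of the log odds ratio: odds ratio (0.38/0.62)/(0.60/0.40) = 0.409, log −0.895; SE = √(1/21.12 + 1/20.73) = 0.309. z = 0.895/0.309 − 1.96 = 0.935, so power is 82.5%.

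Both are within 2 points of the stated 81.98%. At the protocol's minimum detectable odds ratio of 0.43 (60% versus 39.2%), the pooled calculation gives 79.3%.

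**2. Can the cited multiples be used directly?** A 7-fold risk ratio requires a risk of at most 1/7 in women without the factor. With prevalence q, the overall risk is then at most 1/7 + 6q/7, which is 40% at q = 30% and 49% at q = 40%. Neither reaches the assumed 60% recurrence. The multiple can therefore be carried over only as an odds ratio, and doing so is an assumption.

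**3. Simulated power with both predictors added.** Assumptions: 88 per arm; marginal risks 60% and 39.2%; both models contain age > 35 (15% of women, odds ratio 5), BMI > 35 (35%, odds ratio 3) and three null covariates; likelihood-ratio test; 3,000 to 4,000 trials per row. The standard error of one power estimate is about √(0.85 × 0.15 / 4000) = 0.6 points.

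| Prevalence: raised glucose / prior macrosomia | Odds ratios | Listed type of model | With both added | Gain (points) |
|---|---|---|---|---|
| 10% / 10% | 7, 3.5 | 82.9% | 85.6% | 2.7 |
| 20% / 20% | 7, 3.5 | 81.7% | 88.1% | 6.4 |
| 30% / 20% | 7, 3.5 | 82.3% | 88.9% | 6.6 |
| 40% / 30% | 7, 3.5 | 81.0% | 88.5% | 7.5 |
| 20% / 20% | 3, 2 | 83.2% | 85.4% | 2.2 |
| 30% / 20% | 3, 2 | 82.5% | 84.4% | 1.9 |
| 20% / 20% | 2, 1.5 | 83.3% | 84.3% | 1.0 |

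**4. Fasting glucose alone.** At 60% versus 38%, with raised glucose as a yes/no variable at odds ratio 7 and 5,000 trials per row, power goes from 84.8% to 88.9% (+4.1) at 20% prevalence and from 84.5% to 89.7% (+5.2) at 30%.

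With glucose continuous, marginal risks 60% and 39.2%, and a comparison model holding treatment alone:

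| Odds ratio per SD | Wald, without → with | Likelihood ratio, without → with |
|---|---|---|
| 1.3 | 78.6% → 80.7% (+2.1) | 81.6% → 81.0% (−0.6) |
| 1.5 | 78.2% → 81.4% (+3.2) | 81.0% → 81.7% (+0.7) |
| 2.0 | 79.0% → 84.4% (+5.4) | 82.2% → 84.9% (+2.7) |
| 2.5 | 77.1% → 85.3% (+8.2) | 81.0% → 85.8% (+4.8) |

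The two tests differ mainly in the treatment-only model, where the likelihood-ratio test rejects about 3 points more often. A weak predictor yields almost nothing; a strong one yields several points.

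**5. Do the listed covariates do harm?** Three null covariates change likelihood-ratio power from 81.3% to 79.3% (−2.0) and Wald power from 78.4% to 78.9%. Taking three null covariates out once glucose and macrosomia are in changes likelihood-ratio power by at most 86.2% − 85.6% = 0.6 points. Nearly all the gain comes from adding predictors.

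**The case against.** The best defence is that this is a preference and not an error. The word that introduces the list may leave it open, and an analysis plan that is not shown could complete it. The list already holds BMI, age and race/ethnicity, all of which the background section supports. Randomisation is stratified on HbA1c below versus at or above 5.7 ({16a}), so part of baseline glycaemia is balanced by design, and putting that stratum in the model would take up part of any gain. All of this stands, and it limits the point to one of efficiency. It does not remove the point: the article does name covariates for its primary model, none is glycaemic, and whether glucose is in should be settled before the data are seen.

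A reader might infer more than the document supports:

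- **A fixed loss of 5 to 8 points.** This needs the cited multiples to hold as odds ratios among women who all had GDM, and each factor to be present in about 20% or more. The document gives neither, and weaker assumptions give 1 to 3 points.
- **That the protocol ranks prior macrosomia among the strongest predictors.** It ranks nothing in this way. The multiple for macrosomia is below those for age, BMI and HbA1c and exceeds only family history. That it is recorded is inferred from the pregnancy history.
- **That education, income and smoking waste degrees of freedom and should be swapped out.** The background section's silence does not show that they are unrelated to GDM, and step 5 shows that removing them gains almost nothing.
- **That the treatment estimate is biased.** Omitting a baseline predictor from a randomised comparison costs precision. Chance imbalance in glucose among the women who conceive remains possible, but that is a matter of precision too.

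**Conclusion.** The point holds as an efficiency point. The primary model names no baseline glycaemic measure, although fasting glucose is collected, is closely related to the outcome, and is cited with a large risk gradient. Adding it, with prior macrosomia where recorded, is worth about 1 to 8 points of power at 88 per arm. The upper end assumes odds ratios of 7 and 3.5 with prevalences of at least about 20%; the lower end assumes odds ratios near 2 and 1.5. A still weaker predictor would bring the gain close to zero, and including the HbA1c stratum would reduce it. Validity of the primary test is not in question.

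**What to change.** In section {20a}, before outcomes are analysed by group, add baseline fasting glucose as a continuous variable to the named covariates of the primary logistic model. If the pregnancy history records it, a prior macrosomic infant (yes/no) can be added as an optional second variable. Education and income can stay.

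The cost is one or two parameters against about 53 + 33 = 86 expected GDM cases, with no new data collection. Two further items are needed. First, a rule for the few women with missing baseline glucose, because section {20c} deals with missing outcome data and does not cover covariates. Second, the ethics review and registry update that section {25} requires for any change to the analyses.

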### Sample size {14}

Power calculations assume a 60% GDM recurrence rate in women with overweight or obesity [19, 57, 58]. With a target sample size of 252 participants and assumed ≥ 70% pregnancy rate [151, 152] and 30% lost to follow-up or not pregnant before conception, ≥ 176 pregnant participants (≥ 88 in each group) would provide adequate statistical power (≥ 81.98%) to detect intervention effects on the proportions developing recurrent GDM [83, 153], taking into account estimations of site-specific clustering effects and effect modifiers (i.e., weight status, ethnicity, parity) of GDM recurrence [24, 57]. Under this scenario, the minimum detectable effect size (odds ratio) would be 0.43, and proportions with GDM in educational control and intervention groups respectively would be 60% (*n* = 53/88) and 38% (*n* = 33/88). For secondary aims, 88 pregnancies in each group would yield > 80% power to detect effects equal to or smaller than those reported in prior work testing effects of lifestyle interventions on reductions in glucose, triglycerides, CRP [154], insulin, leptin [155], adiponectin [156], and blood pressure [157], taking into account estimations of site-specific clustering effects and effect modifiers (i.e., weight status, ethnicity, parity) of insulin resistance [158], and CVD risk factors [159, 160]. For secondary aims examining effects of the intervention on prenatal and perinatal complications, the study would have > 80% power to detect moderate effect sizes [161]. For the fourth aim examining the effects of the intervention on pre-pregnancy weight losses and improvements in eating (calories, macronutrient balance, fast food) and activity, 88 participants in each group would yield > 90% power to detect effects reported in prior work testing effects of lifestyle interventions on reductions in weight [157] and behavioral variables [162, 163]. For exploratory mediator analyses, > 80% power is achieved to detect > 21% increase in the mediated odds of GDM per kilogram difference in pre-pregnancy weight loss (equivalent to a mediated slope in a logistic model of > 0.189).

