## Assignment of interventions: allocation

### Sequence generation {16a}

Eligible participants are randomized in a 1:1 ratio into the intervention or control group based on a computer-generated (R 4.0.4 for Windows) random sequence. Randomization is stratified by site, pre-diabetes status (HbA1c < 5.7 vs. ≥ 5.7), and prior method of GDM diagnosis (one-step, 2 h test vs. other methods) to ensure a balance of the two interventions within each stratum.

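### The primary logistic model names only one of the three stratification factors: pre-diabetes status and prior GDM diagnostic method should be added to it, for a modest gain in power

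*Protocol article*

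**What the plan says.** Protocol article, Sequence generation {16a}: "Randomization is stratified by site, pre-diabetes status (HbA1c < 5.7 vs. ≥ 5.7), and prior method of GDM diagnosis", the last factor being split into the one-step 2-hour test versus other methods.

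Statistical methods {20a}: "A multiple logistic regression analysis will be used to examine the effect of the treatment group on the proportion of women who develop GDM". On adjustment: "The model will include site and covariates to adjust for pre-randomization variables that may relate to the outcome". Eight such variables are then named in the article, introduced by a word that leaves the list open: "including parity, age, education, income, smoking, race/ethnicity, BMI, and time since last pregnancy". Site is the only stratification factor mentioned. Neither HbA1c nor prior diagnostic method appears here, and no other section adds them to the model.

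The secondary models are described less uniformly. The last sentence of {20a} (composite scores, offspring obesity, gestational weight gain above guideline) carries over the covariate list of the primary model. The mixed models and the models for the individual complications refer only to site and unlisted baseline covariates.

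Risk factors for gestational diabetes: "HbA1c between 5.8 and 6.4 (5- to 8-fold increased risk", among the largest risks that section lists. Education, income and smoking are in the model although the article quotes no risk for them.

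**The concern.** When allocation is balanced within levels of a prognostic factor, the treatment estimate varies less from trial to trial than it would under simple randomisation. A model that leaves the factor out does not see this. Its standard error is too large, its p-value too cautious, and the precision that the stratification bought is not used. In logistic regression, adjusting for a strong predictor of outcome also tends to raise the power of the treatment test.

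Both variables are known for every woman before randomisation, and the design treats both as important enough to stratify on. The planned power is only just above 80%, so a free gain of a few points is worth having.

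**Working it through.** **Inputs from the protocol article.** 252 randomised 1:1; about 70% pregnant and analysed (252 × 0.70 = 176.4, i.e. 88 per group); "Power calculations assume a 60% GDM recurrence rate in women with overweight or obesity"; group proportions "60% (*n* = 53/88) and 38% (*n* = 33/88"); stated power at least 81.98%.

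**Assumed, because the article gives no figure.** Two-sided alpha 0.05; pre-diabetes prevalence 35% (20% and 30% also tried); one-step prior diagnosis in 30%; blocks of 4 within strata; stratum odds ratios from 1 to 8.

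**Step 1: reproduce the stated power.** Pooled two-proportion formula, mean proportion (0.60 + 0.38)/2 = 0.49:

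- null SE = √(2 × 0.49 × 0.51 / 88) = 0.0754
- alternative SE = √((0.60 × 0.40 + 0.38 × 0.62) / 88) = 0.0735
- power = Φ((0.22 − 1.96 × 0.0754) / 0.0735) = Φ(0.98) = 83.7%

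A Wald test on the log odds ratio gives 82.5% and Fisher's exact test 81.8%. All three lie within 2 points of the stated 81.98%, so the figure is reproduced.

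**Step 2: simulate the omission.** Each run randomises 252 women in blocks within site × pre-diabetes × diagnostic method, keeps a random 70%, and fits two logistic models: treatment + site, and treatment + site + the two omitted factors. Overall GDM rates are held at 60% vs 38%, or at 60% in both groups for the null. Prevalence of pre-diabetes is 35%. Each cell uses 12,000 runs, except the power and estimated odds ratios in the last row (4,000).

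| Assumed OR: pre-diabetes / method | Null rejection, without → with | Mean model SE ÷ true SD, without | Power, without → with | Estimated treatment OR, without / with |
|---|---|---|---|---|
| 1 / 1 | 5.3% → 5.6% | 0.3113 / 0.3167 = 0.98 | not run | not run |
| 3 / 1.5 | 4.6% → 5.1% | 0.3113 / 0.3061 = 1.02 | 83.7% → 85.8% | 0.40 / 0.37 |
| 5 / 1.5 | 4.3% → 5.1% | 0.3113 / 0.3038 = 1.02 | 84.6% → 88.5% | 0.40 / 0.34 |
| 8 / 2 | 3.4% → 5.1% | 0.3112 / 0.2926 = 1.06 | 85.5% → 90.3% | 0.40 / 0.31 |

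Monte Carlo error of a null rate at 12,000 runs is √(0.05 × 0.95 / 12,000) = 0.2 points. At odds ratios 2 / 1.5, power goes from 83.5–83.9% to 84.6–85.0%, about 1 point. A separate set of runs at 30% prevalence gave null rejection without the factors of 4.5%, 4.1% and 3.8% at odds ratios 3, 5 and 8, against about 5% with them. Its power gains were about 1 point at odds ratios 2–3 and 3–5 points at 5–8.

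**Step 3: can the 5- to 8-fold figure be carried over?** It cannot be read as a risk ratio for recurrence at the prevalences assumed here. If the lower-HbA1c risk is r, a five-fold ratio needs 5r ≤ 1, so r ≤ 0.20. With prevalence q the overall risk is r(1 + 4q). At q = 35% this is at most 0.20 × 2.4 = 48%, short of the assumed 60%. It is therefore used only as a guide to the upper end of the odds-ratio range.

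**The case against.** The strongest case against is that this is a small and safe-sided inefficiency in a condensed article. Several parts of that case stand.

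- **The list is open.** The covariates are introduced as pre-randomisation variables that may relate to outcome, and HbA1c status fits that description. The wording does not exclude the stratifiers. It does not commit the analyst to them either, and someone fitting the named list would omit them.
- **The simulated model is thinner than the planned one.** It holds only site as a further covariate. BMI and race/ethnicity may carry part of the HbA1c signal, so the real gain may be smaller.
- **The prognostic evidence is indirect.** The 5- to 8-fold figure concerns GDM in general, not recurrence among women who have all had GDM and have BMI of at least 25, and its range starts at 5.8 rather than 5.7. Nothing in the document shows that prior diagnostic method predicts recurrence.

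Four stronger readings are tempting, and the document does not support them:

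- *That the error bars are wrong in a dangerous direction.* They are slightly too wide; false positives are not inflated.
- *That the omission pushes power below 80%.* The article says "the minimum detectable effect size (odds ratio) would be 0.43". From 60%, that gives odds of 0.43 × 1.5 = 0.645, a risk of 0.645/1.645 = 39.2%, and 79.3% power by the formula in step 1. The shortfall comes from the mismatch between 39.2% and the stated 38%: in simulation at 39.2%, power is 78% even when HbA1c has no effect. At 38%, the model without HbA1c keeps 83–85% for stratum odds ratios of 1 to 5.
- *That the odds ratio is biased towards 1.* The shift from about 0.34–0.37 to 0.40 is non-collapsibility: the two models estimate different quantities.
- *That every secondary model shares the omission.* Only the last sentence of {20a} reuses the list. The other models leave their baseline covariates unnamed.

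**Conclusion.** The point holds in a limited form. Two of the three factors that govern the randomisation are not named in the primary model, and one of them is, by the protocol's own account, a strong risk factor for GDM.

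Following the named list costs roughly 1 to 5 points of power: 1 to 2 at stratum odds ratios of 2 to 3, and 3 to 5 at 5 to 8. There is nothing to gain if the factors are not prognostic. Standard errors are about 2 to 5% too wide, reaching 6% in the most extreme scenario. The null rejection rate is about 4 to 4.5% at odds ratios of 3 to 5 and slightly below 4% at 8, instead of 5%. The test of the primary hypothesis remains valid.

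These sizes rest on the assumed prevalences, block size and odds ratios, and are likely upper bounds to the extent that BMI and race/ethnicity stand in for HbA1c. Most of the gain is expected from HbA1c. Diagnostic method belongs in the model because it is a stratification factor, not because the document shows it to be prognostic. The change should be made, but the trial's conclusions would not be unsound without it.

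**What to change.** In section {20a}, name the stratification factors explicitly. For example: *The primary model will include treatment group, the three stratification factors (site, baseline HbA1c below 5.7 versus 5.7 or above, and prior GDM diagnosed by the one-step test versus other methods) and the covariates listed.* Continuous baseline HbA1c may replace the binary stratum if that choice is also fixed in advance. State that the same set serves as the baseline covariates of all secondary models.

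The cost is one or two sentences and two model parameters. Both variables are already recorded, since randomisation needed them. The change should be made before unblinded analysis, through the route in the section on protocol amendments {25} (ethics review and a registry update), so that it cannot be taken for a post hoc choice.

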### Preconception weight loss to reduce gestational diabetes and associated health risks

Observational research suggests that women who experience even modest weight losses (> 10 pounds) [33, 34, 83] or less weight gain [84–86] prior to pregnancy significantly reduce their risk of GDM development compared to women who maintain weight or gain > 10 pounds. Kim et al. [48] estimated that up to half of GDM cases could be prevented by reducing pre-pregnancy obesity. Retrospective data from bariatric surgery populations also suggest that weight loss in women with obesity prior to pregnancy may reduce the risk of GDM and its recurrence [37, 87, 88] and prevent transmission of obesity to children [36]. Other observational research has shown that maternal consumption of healthy food and avoidance of unhealthy foods [89] and engagement in regular physical activity before pregnancy were independently associated with reduced risk of subsequent GDM [89]. Honein et al. [90] estimated that if 10% of women with pre-pregnancy obesity achieved a healthy weight (BMI < 25) before pregnancy, nearly 300 congenial heart defects and 700 fetal deaths per year could be prevented each year.

However, few clinical trials have examined the effects of weight loss during the preconception period on subsequent outcomes [41, 91]. The PREPARE randomized trial [41] tested a phone-based weight loss intervention in 326, non-Hispanic (94%) women with a BMI ≥ 27 and found that, relative to the control group, women in the lifestyle intervention lost more weight prior to conception (3.7 vs. 0.6 kg, respectively). After 24 months, 169 (52%) became pregnant and were included in the analysis. The results indicated that those in the preconception intervention group surprisingly gained more weight during their subsequent pregnancy than those in the control group (13.2 vs. 10.3 kg gain, respectively; *p =* 0.03); there were no significant differences in GDM or other pregnancy outcomes, with the exception of spontaneous pregnancy losses, which were less common in the intervention arm. Participants in the intervention arm had a 10% lower absolute rate of GDM than in the control arm (25% vs. 35%, respectively), but the study had insufficient power to evaluate whether or not a difference of this size was due to chance.

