### Objectives {7}

The Gestational Diabetes Prevention/Prevención de la Diabetes Gestacional is a two-site randomized clinical trial testing the efficacy of a pre-pregnancy lifestyle intervention to reduce GDM recurrence in women with overweight and obesity. The trial is following the CONSORT guidelines [103]. The primary hypothesis is that the recurrence of GDM will be reduced among participants assigned to pre-pregnancy lifestyle intervention vs. educational control group. Test for GDM will be conducted at 24 to 28 weeks’ gestation. Secondary hypotheses are that the pre-pregnancy lifestyle intervention (vs. educational control group) will result in improved maternal fasting glucose and biomarkers of insulin resistance (insulin, leptin, TNF-alpha, C-reactive protein, and adiponectin) and CVD risk (lipids and blood pressure) assessed before pregnancy, after 16 weeks of intervention, and at 26 weeks’ gestation. The pre-pregnancy lifestyle intervention (vs. educational control group) is expected to reduce adverse perinatal health outcomes for mothers (gestational hypertension, preeclampsia, preterm delivery, excessive gestational weight gain, induction of labor, cesarean delivery) and neonates (admission to the neonatal nursery, hyperbilirubinemia, birth trauma, weight for length *z*-scores ≥ 95% at birth and 6 weeks). Also, the pre-pregnancy lifestyle intervention (vs. educational control group) is hypothesized to result in greater pre-pregnancy weight loss and improvements in diet (calories, % fat, fast food) and physical activity (minutes of moderate activity). In exploratory mediator analyses, treatment-related changes in pre-pregnancy weight, eating, and activity are expected to be related to improvements in maternal physiology and reduced odds of GDM recurrence.

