## Assignment of interventions: blinding

### Who will be blinded {17a}

Research assistants are masked to randomization, and participants do not know the assigned group until after baseline measures are completed.

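### The mixed model for the secondary outcomes lists no treatment-by-time term, so its one treatment coefficient does not estimate pre-pregnancy change

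*Protocol article*

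**What the plan says.** The section on statistical methods for primary and secondary outcomes {20a} gives one model for weight, eating, activity and physiologic measures: "a linear mixed model with fixed effects for treatment condition (the between-groups factor), time (baseline, 16 weeks, 26 weeks" of gestation, then "site, and baseline covariates". Baseline is therefore a level of the time factor and an outcome row. No interaction and no change contrast is named there or elsewhere in the article. It is also not stated whether the baseline value of each outcome is among the covariates.

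The Objectives {7} set two kinds of target. For weight and behaviour the intervention "is hypothesized to result in greater pre-pregnancy weight loss and improvements in diet" and physical activity, which is a change before pregnancy. The biomarkers are "assessed before pregnancy, after 16 weeks of intervention, and at 26 weeks" of gestation. The Abstract also describes secondary outcomes as changes over time.

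**The concern.** A model with treatment and time as main effects assumes the same group difference at every visit. That cannot be true here. Allocation is randomised, and "participants do not know the assigned group until after baseline measures are completed", so the expected difference at baseline is zero. The 16-week visit shows the effect of the weight-loss programme before pregnancy. The third visit falls in pregnancy, after intervention contacts have stopped at conception.

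One coefficient pooled over these three visits answers neither the pre-pregnancy question nor the in-pregnancy question. It pulls a real 16-week effect towards zero. At stake are the estimates and tests for all weight, diet, activity and cardiometabolic outcomes. An analyst who adds the interaction only after seeing the data would be making a post hoc choice of contrast.

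**Working it through.** **The plan's own figure.** Sample size {14} claims more than 90% power for the weight and behaviour aim: "88 participants in each group would yield" it. This cannot be reproduced, because no effect size, SD or significance level is given. For scale only, a plain two-mean comparison at two-sided 0.05 (assumed) reaches 90% power at (1.960 + 1.282) × √(2/88) = 0.489 SD.

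**Inputs**
- True group differences: 0 at baseline, d at 16 weeks, q·d at 26 weeks' gestation. The document does not give q, so it is varied from 0 (effect gone) to 1 (effect fully kept).
- Share seen at 26 weeks' gestation: 100%, or 70% as in the pregnancy rate assumed under Sample size {14}, taken as equal between arms and unrelated to the outcome.
- Within-person correlation ρ and its structure: not given, so varied. Variances are taken as equal.

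**Formula.** The generalised least squares coefficient is a weighted mean of the three differences. The weights are proportional to the row sums of the inverse covariance matrix, averaged over the missing-data patterns. Dilution is 1 minus coefficient/d.

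**Compound symmetry, complete data.** The weights are equal, so the coefficient is d(1 + q)/3.
- q = 1: 0.667d, dilution 33%
- q = 0.5: 0.500d, dilution 50%
- q = 0: 0.333d, dilution 67%

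**Compound symmetry, 70% seen at 26 weeks' gestation.** Baseline and 16 weeks each get weight 0.7/(1 + 2ρ) + 0.3/(1 + ρ), and the last visit gets 0.7/(1 + 2ρ). At ρ = 0.5 these are 0.55, 0.55 and 0.35, or shares of 0.379, 0.379 and 0.241.
- q = 1: 0.621d, dilution 38%
- q = 0: 0.379d, dilution 62%

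Raising ρ to 0.95 changes these by less than one percentage point.

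**AR(1), complete data.** With the visits treated as equally spaced, the weights are proportional to 1, 1 − ρ and 1.
- ρ = 0.5: weights 0.4, 0.2, 0.4; dilution 40% (q = 1) to 80% (q = 0)
- ρ = 0.95: dilution 49% (q = 1) to 98% (q = 0)

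With 70% seen at the last visit and ρ from 0.5 to 0.95, the figures are 43–49% at q = 1 and 72–84% at q = 0.

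**What this can do to power (illustration).** Take an effect that has 90% power at 16 weeks in a baseline-adjusted comparison with 88 per group: D = 3.242 × √((2/88)(1 − ρ²)). The pooled coefficient D(1 + q)/3 has standard error √((2/88)(1 + 2ρ)/3), under compound symmetry with complete data.
- ρ = 0.5: D = 0.423 SD, standard error 0.123; power 63% (q = 1), about 40% (q = 0.5), 21% (q = 0)
- ρ = 0.9: power 16%, 11% and 7%

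**Can q be well below 1?** The Introduction cites a preconception trial in which "women in the lifestyle intervention lost more weight prior to conception": 3.7 − 0.6 = 3.1 kg. The intervention arm then gained 13.2 − 10.3 = 2.9 kg more during pregnancy. By the end of pregnancy q would be 0.2/3.1 = 0.06. If the reversal accrues linearly to 26 of 40 weeks (an assumption), q = (3.1 − 2.9 × 0.65)/3.1 = 0.39. Dilution with complete data would be about 65% and 54%. This is another trial in another population, so it shows only that q = 1 cannot be taken for granted.

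**After the change.** With treatment-by-time, the 16-week contrast estimates d without dilution and the 26-week effect is estimated separately. Moving baseline to a covariate while keeping one pooled coefficient is not enough. It gives d(1 + q)/2, a dilution of 0%, 25% and 50% at q = 1, 0.5 and 0.

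**The case against.** The strongest reply is that the article lists factors, not a full model. It nowhere says main effects only. Naming a between-groups factor beside a three-level time factor is common shorthand for a group-by-time design, and outcomes described as changes over time imply that contrast. Interactions and covariance structure are often left to an analysis plan, and none is shown here. It stands that the full plan may contain the term and that the intent is probably right. But the article does not leave the model open. It lists the fixed effects, and that list followed as written gives the wrong quantity.

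The reply is also right on several stronger readings that a reader might infer:
- *A single dilution figure, such as 40–60%.* The document gives no correlation, covariance structure or visit-specific effects, so only a range with its assumptions can be stated.
- *That the claimed power of more than 90% is mostly lost.* Its effect sizes come from sources that are not shown, so the loss from that claim cannot be quantified. The power figures above are illustrations.
- *That counting 88 per group for pre-pregnancy outcomes is an error.* It is conservative. The restriction to confirmed pregnancies under {20c} is stated for the primary analysis only.
- *That the last weight before conception should be the endpoint.* Brief visits may be by phone or video, and the timing of that weight is set by conception, an event after randomisation. The documents do not make it the better choice.

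**Conclusion.** The point holds for the model as listed. Its only treatment coefficient mixes an expected zero with one pre-pregnancy and one in-pregnancy difference, and does not estimate the hypothesised pre-pregnancy change. In the main-effects model with q between 0 and 1, dilution relative to the 16-week effect is at least about one third in every case checked. The ranges are 33–67% under compound symmetry with complete data, 38–62% with 70% seen at 26 weeks' gestation, and about 40–98% under AR(1) with ρ from 0.5 to 0.95. All rest on assumed correlation, an assumed q and equal attendance between arms. If the baseline outcome value were also a covariate while baseline stays an outcome row, the weighting would shift further, and dilution could exceed these ranges.

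A reader might infer that the trial's main result is at risk. It is not: GDM recurrence is analysed by a separate logistic regression. This is a correction to the secondary analyses that should be made before the data are analysed.

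**What to change.** State the fixed effects as treatment, time and treatment-by-time, with the baseline mean constrained equal between arms. Alternatively, take baseline out of the outcome rows, use it as a covariate and keep visit-specific treatment effects. Name two contrasts and test them separately: the 16-week contrast in all randomised women with data, and the 26-week gestation contrast. Say which one tests each secondary hypothesis; for weight, diet and activity it is the 16-week contrast. If the full analysis plan already does this, align the published description with it.

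The cost is a few lines of analysis wording. No new data, visits or participants are needed.
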